### Description of Processes, Interventions, and Comparisons

The patients randomized to the intervention group will benefit from a foot reflexology session (30 minutes) at each chemotherapy session for four cycles. The reflexology sessions will be given during chemotherapy infusion every 2 or 3 weeks, depending on the chemotherapy protocol. The sessions will be administered by two qualified reflexologists (they were trained at the French school École des Techniques en Réflexologie).

In a meta-analysis study, Lee et al [28] determined that the optimal comparator is a control group with conventional care without foot reflexology or massage therapy.

Foot reflexology is CAM, based on the principle of acupressure, that helps the body restore homeostasis. It is a holistic approach that allows one to understand the body as a whole. Each part of the body is represented by a zone or reflex point on the foot. The reflexologist stimulates each reflex zone using specific thumb and finger techniques on the patient’s feet. Depending on the objective, the zones on the feet are stimulated using different types of pressure. During a session focused on the treatment of CINV, the reflexologist mainly stimulates the reflex points related to the digestive system, the lymphatic system, and kidneys to help the body eliminate toxins. The reflexology chart used in this clinical study is based on the one proposed by Eunice Ingham [29].

The reflex zones of the whole body are also found on the hands. During the first reflexology session, the reflexologist shows the patient the appropriate zones on the hands to relieve nausea. The patient will be able to stimulate these reflex points between each cycle if necessary (self-practice at home). Adherence of participants to reflexology is assessed with a diary. They have been instructed to use a diary every day between each cycle of chemotherapy to note episodes of nausea and vomiting. They also note if they took at least one antiemetic drug (on-demand treatment). If the patient uses self-massage, they note whether it has been effective.

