### Enrolment, Screening, and Allocation

Participants will be enrolled by physicians at the Lyon Sud Hospital Centre thoracic and hepatogastroenterology departments. Eligible participants who wish to participate in the study are asked to sign a written informed consent form. The randomization procedure is performed by the Interactive Web Response System (IWRS) via ClinSight software (Ennov Clinical, version 7.5.710, Ennov Group). Participants are allocated to the intervention group (with foot reflexology) or to the control group (without foot reflexology) before starting their treatment. Clinical research assistants generate the random allocation sequence and assign participants to the intervention.

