### Evaluation Criteria

#### Primary Outcome

The primary outcome is the relative change in the severity of nausea and vomiting, as assessed with a visual analogue scale (VAS). The patient is asked to mark their current nausea level on the horizontal line with anchor statements on the left (a happy face, no nausea=0 mm) and on the right (a very sick green face, paroxysm of nausea or vomiting=100 mm). Unlike vomiting, which is measurable by the number of episodes per day, nausea is a subjective experience. For that reason, we will use a VAS to evaluate the severity of nausea in patients [30]. For patients in the intervention group, this measurement will be done when the patient arrives at the outpatient or inpatient department and after the foot reflexology session, during the second cycle of chemotherapy. For patients in the control group, this measurement will be done when the patient arrives at the outpatient or inpatient department and before leaving the hospital, during the second cycle of chemotherapy. The assessment is performed by a nurse or clinical research assistant.

All patients will continue to receive standard antiemetic drugs (eg, 5-hydroxytryptamine 3 receptor antagonists, dexamethasone, and neurokinin-1 inhibitor receptor antagonists). According to chemotherapy protocols, oral antiemetic agents are included, and patients are instructed to complete the course.

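### The primary VAS change is measured from cycle-2 arrival, after randomisation and session 1, so it shows the same-visit effect of session 2 rather than the total effect on CINV

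*Protocol article*

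**What the plan says.** All references are to the protocol article.

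- **Allocation.** Under Enrolment, Screening, and Allocation, patients are allocated "before starting their treatment".
- **Intervention.** Under Description of Processes, Interventions, and Comparisons, the reflexology arm "will benefit from a foot reflexology session (30 minutes) at each chemotherapy session for four cycles". The same section adds: "During the first reflexology session, the reflexologist shows the patient the appropriate zones on the hands to relieve nausea". It continues: "The patient will be able to stimulate these reflex points between each cycle if necessary (self-practice at home").
- **Endpoint.** Under Primary Outcome: "The primary outcome is the relative change in the severity of nausea and vomiting, as assessed with a visual analogue scale (VAS"). The scale is momentary: "The patient is asked to mark their current nausea level on the horizontal line".
- **Timing.** For the reflexology arm, "this measurement will be done when the patient arrives at the outpatient or inpatient department and after the foot reflexology session", at cycle 2. For controls the second mark is made "before leaving the hospital, during the second cycle of chemotherapy".
- **Analysis.** Type of Statistical Analysis Used compares relative change between arms in a linear model adjusted for cancer type and metastases. No VAS before randomisation or at cycle 1 is described.
- **Objective.** Primary Objective refers to benefit on CINV from platinum-based chemotherapy, without restriction to a single visit.

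**The concern.** In a change-from-baseline endpoint the reference is normally fixed before treatment, so that randomisation balances it. Here it follows session 1 and, for some patients, two or three weeks of self-practice. If either lowers nausea, the arrival mark is lower in the reflexology arm and the ratio is taken against a value that treatment has already improved.

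Three consequences follow.

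1. The primary result does not address the objective as worded. Benefit between cycles, which self-practice is meant to provide, can appear as no difference.
2. Relative change is undefined at an arrival mark of 0 mm. If treatment brings more reflexology patients to 0 mm on arrival, the patients with a defined ratio may differ by arm because of treatment.
3. Replacing the ratio with a model adjusted for arrival VAS would not resolve this, because that model would still condition on something treatment can change.

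The other relative-change endpoints are set up differently: QLQ-C30 and HADS are each measured at baseline and at the fourth cycle.

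**Working it through.** **Order of events.** Randomisation → cycle 1 with session 1 and teaching of hand zones → interval of 2 or 3 weeks with optional self-practice → cycle-2 arrival VAS (reference) → session 2, or usual care → second VAS. The reference comes fourth in this chain.

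**The plan's own figure.** Inputs from Sample Size: mean improvement 49.5% v 73.5% (difference 24.0), SD 32.2, two-sided 5%, power 90%.

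n per arm = 2 × (1.960 + 1.282)² × 32.2² / 24.0² = 37.8, so 38; the t-test version gives 39. At 40 per arm power is 91.5% (normal) or 90.9% (t). The stated 40 reproduces, and the sample-size arithmetic is not at fault.

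**What carry-over does to the endpoint.** Let the arrival VAS without treatment be 1, and let the reflexology arm arrive at 1 − c. The value of c is an assumption, because the documents give none.

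*Case A: all benefit is gained before arrival.* The final mark is 0.505 of arrival in both arms. The planned difference is 0 points for every c. Measured against the untreated arrival level the difference would be 0.505c, for example 10.1 points at c = 20% and 20.2 points at c = 40%.

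*Case B: the total benefit is the planned 24 points, part of it already present on arrival.* Final marks are 0.505 (control) and 0.265 (reflexology). The visible difference is (1 − 0.265/(1 − c)) − 0.495 = 0.505 − 0.265/(1 − c). Power uses SD 32.2 and 40 per arm, so the standard error is 32.2 × √(2/40) = 7.20 points.

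| c | Visible difference (points) | Power |
|---|---|---|
| 0% | 24.0 | 91.5% |
| 10% | 21.1 | 83% |
| 20% | 17.4 | 67% |
| 30% | 12.6 | 42% |
| 40% | 6.3 | 14% |

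**Patients with a defined ratio.** As an illustration only: if 30% of controls and 40% of reflexology patients arrive at 0 mm, 40 × 0.70 = 28 and 40 × 0.60 = 24 contribute. The documents give no share of zeros in either arm.

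**The case against.** The case for leaving the plan alone has substance.

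- **Carry-over may be small.** It would have to last 2 or 3 weeks on a scale of present nausea, and self-practice is used only if needed. This stands: the size of the problem is assumed, not shown.
- **A same-visit endpoint is a legitimate choice.** The protocol says the time point was chosen to limit missing data. This also stands, but the objective and conclusions should then say what is being estimated.
- **The diary covers the time between cycles.** It records frequency and peak intensity daily, and the abstract mentions frequency alongside severity. This fills the gap only in part, because the diary is listed as secondary and uses a different scale.
- **The error is towards the null in the cases shown.** No inflation of false positives is demonstrated.

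Two stronger readings are tempting and are not supported.

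*A reader might infer that the endpoint cancels every benefit of reflexology.* It does not. Removal is complete only when arrival and final marks are scaled by the same factor. Otherwise it is partial and its direction can vary, for instance near the floor of the scale. Any effect of session 2 itself is still measured.

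*A reader might infer that end-of-visit VAS would make a more powerful primary outcome.* This was checked in 4,000 simulated trials under assumed distributions: 40 per arm, 30% at 0 mm in both arms, the rest gamma with shape 1.5 and mean 30 mm, and a log-normal within-visit factor with log-SD 0.6. With the planned 49.5% v 73.5% session effect and no carry-over, relative change rejects in about 94% of trials and a rank test on final VAS in about 24%. With 33% carry-over, equal zeros and no session effect, final VAS rejects in only about 12%. These figures depend on the assumed spread, but they rule out a general claim that a swap gains power. A reference mark at the start of cycle 1 is not clearly better either, since chemotherapy-induced nausea may hardly have begun.

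**Conclusion.** The point holds as a mismatch between endpoint and claim. The reference for the primary relative change is a post-randomisation value, taken after session 1 and optional self-practice. The result therefore speaks to the second session's effect within one visit, while the Primary Objective and the conclusions speak of CINV in general.

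The timing facts are certain from the text; the magnitude is not. The fall to between 21 and 6 points, with power between 83% and 14%, rests on three assumptions: carry-over of 10 to 40%, a total benefit of exactly 24 points, and an unchanged SD of 32.2. With no carry-over nothing is lost. Differing sets of evaluable patients are a possibility that follows from the design; the documents do not show that it will occur. The material supports clarifying the claim and adding analyses. It does not support replacing the primary endpoint.

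**What to change.** 1. In Primary Objective, Primary Outcome and the conclusions, state that the primary VAS outcome estimates the same-visit effect of the reflexology session at cycle 2, and not the total effect on CINV.
2. In Type of Statistical Analysis Used, prespecify two further between-arm comparisons in millimetres: cycle-2 arrival VAS and cycle-2 end-of-visit VAS. Include all randomised patients with a mark, counting those at 0 mm. Adjust only for cancer type and metastases, not for arrival VAS.
3. Interpret the primary result alongside both. A lower arrival VAS with reflexology would signal that the relative change understates benefit. It would also warn that the patients with a defined ratio may not be comparable.

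These comparisons should be described as supporting, without any claim that end-of-visit VAS has more power. The end-of-visit comparison also keeps the plan's different timing of the second mark in the two arms.

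The cost is two extra analyses of data already collected and a narrower primary claim. No new patients or measurements are needed, and the sample-size basis is untouched.

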### Eligibility Criteria of Participants

Eligibility requirements for this study are the following: patients aged ≥18 years; patients with lung cancer (eg, non–small cell lung carcinomas, small cell lung cancer, mesothelioma) or digestive system cancer (eg, colorectal cancer, pancreatic cancer, liver cancer); patients on platinum-based chemotherapy with or without radiation therapy concomitant (eg, digestive system cancer: FOLFOX, FOLFIRINOX, GEMOX, LV5FU2-CDDP; lung cancer: cisplatin-vinorelbine, pemetrexed-cisplatin, pemetrexed-carboplatin, carboplatin-paclitaxel); World Health Organization performance status ≤2; patients affiliated to the national social security system or equivalent; patients able to complete the questionnaires (comprehension of oral and written French language); and patients who provide written informed consent. The exclusion criteria are phlebitis; vena cava syndrome; weight loss >5% in the 3 months before inclusion date; uncontrolled pain; patients receiving morphine or morphine derivatives; brain metastases; patients receiving foot reflexology outside the study; patients under guardianship or curatorship or who have been deprived of their rights. All data will be collected from outpatients and inpatients.

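### The second primary VAS reading is tied to a different event in each arm, so time of measurement is confounded with treatment

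*Protocol article*

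**What the plan says.** The Primary Outcome section of the protocol article sets the first VAS at the same moment in both arms: "this measurement will be done when the patient arrives at the outpatient or inpatient department". The second VAS follows a different rule in each arm:

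- **Reflexology arm:** the readings are on arrival at the "department and after the foot reflexology session, during the second cycle of chemotherapy".
- **Control arm:** the readings are on arrival at the "department and before leaving the hospital, during the second cycle of chemotherapy".

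The scale is momentary: "The patient is asked to mark their current nausea level on the horizontal line".

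The section Description of Processes, Interventions, and Comparisons places the 30-minute sessions within the infusion: "The reflexology sessions will be given during chemotherapy infusion every 2 or 3 weeks, depending on the chemotherapy protocol". The Eligibility Criteria section adds that "All data will be collected from outpatients and inpatients", so the time of departure can belong to a day visit or to an admission.

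The primary model, in Type of Statistical Analysis Used, adjusts for cancer type and metastases only.

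**The concern.** A rating of current nausea depends on when it is taken. The reflexology reading is anchored to a session held during the infusion. The control reading is anchored to departure, which normally comes after the infusion and for an inpatient could come much later. Time since the start of platinum, and since that day's antiemetics, therefore differs between arms by rule and not by chance.

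Randomisation balances the patients but not a measurement rule that depends on the arm. A larger trial would only estimate the same biased contrast more precisely. Any change in nausea between the two moments enters the estimated treatment effect, so a positive or a negative primary result could partly or wholly reflect time of measurement. The van Elteren fallback and the per-protocol analysis use the same readings and inherit the problem.

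**Working it through.** **Inputs** (Sample Size section): mean improvement 49.5% and 73.5%, so a difference of 73.5 − 49.5 = 24 percentage points; common SD 32.2%; two-sided 5%; power 90%; 40 per group.

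**The plan's own figure.**

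- Normal approximation: n per group = 2 × (1.960 + 1.282)² × 32.2² / 24² = 37.8, rounded up to 38.
- The t-test version gives 38.8, rounded up to 39.
- At 40 per group, power is 91.5% (normal) or 90.9% (t).

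The stated 40 is consistent with the stated inputs, so the sample size is not at issue.

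**Precision of the primary contrast.** SE = 32.2 × √(2/40) = 7.20 percentage points. An observed difference of about 1.96 × 7.20 = 14.1 points is significant.

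**Effect of a timing difference.** Let b be the mean shift in relative change produced only by the different reading times, in percentage points, with the SD unchanged. The documents give no value for b, so the values below are assumptions.

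- With no true effect: P(reject) = Φ(b/SE − 1.96) + Φ(−b/SE − 1.96).
- With a true effect of 24 points and timing working against reflexology: power is computed at a difference of 24 − b.

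| b (percentage points) | Rejection rate, no true effect | Power, true effect 24, bias against reflexology |
|---|---|---|
| 0 | 5.0% | 91.5% |
| 3 | 7.0% | 83.1% |
| 5 | 10.7% | 75.1% |
| 8 | 19.9% | 60.3% |
| 10 | 28.4% | 49.4% |
| 12 | 38.5% | 38.5% |
| 15 | 54.9% | 23.9% |

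**Unit.** These are points of relative change, not millimetres on the scale. For illustration, a 5 mm shift is 5/50 = 10 points for a patient who arrives at 50 mm, and 5/20 = 25 points for one who arrives at 20 mm. A small movement on the line can therefore be a large b when arrival scores are low.

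**Is the difference offset elsewhere?** The article describes no matched rest period for controls, no common clock time for the second reading, and no time variable in the primary model.

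**The case against.** The strongest reply is that the article gives no actual times. It says the reading follows the session, without saying how soon, and that the session falls within the infusion, without saying where. An outpatient whose session comes late in the infusion and who leaves soon afterwards might be scored at nearly the same moment as a control. This stands: the size of the gap is unknown, and longer exposure in controls is an inference that will hold for most patients but is not a documented fact. It does not remove the problem, because nothing requires the two moments to coincide.

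The direction is also open. More time since chemotherapy could raise nausea at the control reading, while more time under antiemetic cover could lower it. This stands too, and it is why the table shows both false rejection and lost power. An unknown direction leaves either result hard to interpret.

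The values of b are illustrative, and the lower ones have modest effects. The table should not be read as an estimate of the trial's actual error rate.

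Finally, the daily diary and its Poisson analysis use the same recording rule in both arms, so that comparison of nausea and vomiting is free of this fault. It is a secondary outcome, however, and does not repair the primary one.

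The point cannot be left to a fuller protocol or analysis plan, because the article itself states the two different time points.

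**Conclusion.** The concern holds. As written, the primary contrast cannot separate the effect of reflexology from the effect of when nausea was scored. The arm-dependent rule is certain from the text; the size and direction of the bias are not.

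On the assumption that timing shifts the mean relative change by 5 to 15 points with the SD unchanged, the nominal 5% test would reject in 11% to 55% of trials with no true effect. If the shift ran against reflexology, power for the planned effect would drop to between 75% and 24%. All these shifts are smaller than the 24 points the trial is designed to detect. This should be corrected because it affects the validity of the primary endpoint.

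**What to change.** Define the second VAS by one rule for both arms. Two choices are workable: before departure in everyone, or at a fixed interval after infusion start, set so that the session is over by then. The fixed interval has the advantage of removing the variation in length of stay between outpatients and inpatients. Record the clock time of infusion start and of every VAS mark. Keep the post-session mark in the reflexology arm as an additional, descriptive reading.

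The cost is one VAS mark moved or added and a time stamp. The sample size stays at 40 per group. The downside is that a later reading may show a smaller immediate effect than one taken after the session.

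The article reports that enrolment began in June 2018 and plans the analysis for the second quarter of 2020, so some data may already exist. For those patients, if times were recorded, report their distribution by arm and add minutes from infusion start to the second VAS as a covariate in a sensitivity analysis. This is only a limited check: time and arm may barely overlap, so the adjustment would rest on extrapolation. State the limitation beside the primary result, and show the diary comparison next to it.

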#### Secondary Outcomes

##### Nausea and Vomiting

The benefits of foot reflexology on CINV will also be assessed with the diary completed every day by patients between the first and fourth cycle of chemotherapy. Every day, the patient assesses the frequency of nausea and vomiting, recording each episode of nausea and emesis, and assessing the intensity of nausea and vomiting when it is at its highest with a Likert scale (response modalities: “Very low,” “Low,” “Low Moderate,” “Severe,” “Very severe,” “Unbearable”).

##### Quality of Life

The benefits of foot reflexology on quality of life will be assessed by the relative change in the overall European Organization for Research and Treatment of Cancer Quality of Life Questionnaire (EORTC QLQ-C30) score [31]. The patient is asked to complete EORTC QLQ-C30 at the baseline and end of the study (fourth cycle of chemotherapy).

##### Anxiety

The benefits of foot reflexology on anxiety will be assessed by the relative change in the overall Hospital and Anxiety Depression Scale (HADS) score [32]. The patient is asked to complete HADS at the baseline and end of the study (fourth cycle of chemotherapy).

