### Secondary Objectives

The secondary objectives are to assess the benefits of foot reflexology in terms of overall quality of life, anxiety, and self-esteem.

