##### Self-Esteem

The benefits of foot reflexology on the level of self-esteem will be assessed at the end-of-study visit using the Body Image Questionnaire (BIQ) [33], which measures body image at a given time. The analysis of the BIQ takes into account the level of self-esteem assessed at the baseline using the Rosenberg scale [34].

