## Discussion

According to a European survey reported by Molassiotis et al [1], 35.9% of patients with cancer use CAMs, and after a diagnosis of cancer the use of CAMs increases by at least 30%. For varied reasons, some patients do not inform caregivers or health care professionals that they use CAMs [37,38]; however, certain CAMs could have potential interactions with conventional cancer treatments [39,40]. In parallel, oncologists lack adequate information about the safety and efficacy of CAMs to confidently inform their patients [41-43] and they have requested more rigorous evaluation [42,43]. Moreover, the World Health Organization’s Traditional Medicine Strategy emphasizes the importance of thorough evaluation; the objectives of this strategic approach are to inform policy; determine safety, efficacy, and quality; increase access; and promote the rational use of traditional medicine [44].

This RCT (Clinicaltrials.gov identifier: NCT03508180), which began in June 2018, assesses the benefits of foot reflexology. The expected results are a decrease in CINV and anxiety, as well as an improvement in quality of life and self-esteem. This will also allow the investigation of any potential difference in benefit between patients with lung cancer and patients with digestive system cancer, and patients with different stages of cancer (metastatic and nonmetastatic). The results will be available in the last quarter of 2020.

This study does have limitations. First, the results may not be representative of all cancers; patient recruitment was only done at one cancer center. Even if conventional treatments are similar within the various private and public health care centers in France, a larger multicenter study would ensure that the results are generalizable.

In conclusion, the current management of patients with cancer involves treatment with conventional medicine while offering supportive oncological care. If the results of this study are significant, foot reflexology may be a promising complement to conventional antiemetic drugs.

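### Two secondary outcomes do not match their objectives: self-esteem is assessed with a body-image questionnaire, and the overall HADS score does not isolate anxiety

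*Protocol article*

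**What the plan says.** The Secondary Objectives section reads: "The secondary objectives are to assess the benefits of foot reflexology in terms of overall quality of life, anxiety, and self-esteem".

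**Self-esteem.** Under Secondary Outcomes, the Self-Esteem section places the assessment at the end-of-study visit, "using the Body Image Questionnaire (BIQ) [33], which measures body image at a given time". It continues: "The analysis of the BIQ takes into account the level of self-esteem assessed at the baseline using the Rosenberg scale". The statistical analysis section describes the matching comparison as one of self-image, made by a linear model with the baseline Rosenberg score as covariate.

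**Anxiety.** The Anxiety section says: "The benefits of foot reflexology on anxiety will be assessed by the relative change in the overall Hospital and Anxiety Depression Scale (HADS) score". HADS is completed at baseline and at the fourth cycle. The statistical analysis section assigns anxiety a Wilcoxon test and names no anxiety subscore.

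**Expected result.** The Discussion anticipates "a decrease in CINV and anxiety, as well as an improvement in quality of life and self-esteem".

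**The concern.** An outcome should measure what its objective names. Here one outcome measures a different construct and the other mixes two constructs.

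If the plan is followed as written, a group difference in body image would be reported as a benefit on self-esteem. A difference in a combined anxiety and depression score would be reported as a benefit on anxiety, even if it came wholly from the depression items. Conversely, a real effect confined to anxiety could be weakened by items that did not move. The Discussion already states the expected conclusions in terms of anxiety and self-esteem, so the mislabelling would carry into the interpretation.

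**Working it through.** **1. Self-esteem: the statements side by side.** No arithmetic applies.

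| Item | Where | Construct | When |
|---|---|---|---|
| Objective | Secondary Objectives | self-esteem | – |
| Rosenberg scale | Self-Esteem | self-esteem | baseline |
| BIQ | Self-Esteem | body image (the protocol's own description) | end of study |
| Analysis | statistical analysis section | self-image (BIQ score), Rosenberg as covariate | end of study |
| Expected result | Discussion | improvement in self-esteem | – |

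The Abstract's list of instruments for the secondary objectives (EORTC QLQ-C30, HADS, BIQ) does not include the Rosenberg scale, which agrees with its use as a covariate only. A treatment effect on self-esteem needs self-esteem measured after randomised treatment, and none is described. Neither a larger sample nor another model can supply it.

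**2. Anxiety: what the total can show.** The documents give no figures for HADS, so the inputs are assumptions:
- an anxiety part A and a depression part D with equal standard deviation σ;
- a correlation r of 0.5 to 0.7 between them;
- treatment shifts A by δ standard deviations and D by k × δ.

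The variance of A + D is 2σ²(1 + r), and the mean of the total shifts by (1 + k)δσ. So

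standardised effect on total ÷ effect on A = (1 + k) / √(2(1 + r)).

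| Shift in depression | r = 0.5 | r = 0.6 | r = 0.7 |
|---|---|---|---|
| none (k = 0) | 1/√3.0 = 0.577 | 1/√3.2 = 0.559 | 1/√3.4 = 0.542 |
| half (k = 0.5) | 0.866 | 0.839 | 0.813 |
| equal (k = 1) | 1.155 | 1.118 | 1.085 |

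In the first row, the squared factors are 0.33 to 0.29, the share of the information kept when only anxiety moves. In the last row the total is more sensitive than the anxiety part.

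By symmetry, a shift of δ in depression alone, with no change in anxiety, gives the same effect on the total as the first row: 0.54δ to 0.58δ. The total cannot tell these two situations apart. That conclusion needs neither the assumed r nor the assumed variances, only that the score pools both kinds of item.

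**3. The plan's own figure.** The only sample-size figure concerns the primary VAS endpoint. With a difference of 73.5 − 49.5 = 24 points, SD 32.2, two-sided 5% and 90% power, n = 2(1.960 + 1.282)² × (32.2/24)² ≈ 37.8, so 38 per group (39 by the t-test). The stated 40 is consistent with this. It neither supports nor weakens the present point.

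**The case against.** - **The anxiety objective is measured.** A reader might infer that two of the three secondary objectives go unmeasured. For anxiety the text does not support that: the overall HADS contains anxiety and is collected at both time points. The fault is that the score does not isolate anxiety.
- **The analysis plan may report subscores.** It is not shown and may do so. But the protocol does not leave the anxiety score open; it fixes the overall one. Nor can an analysis plan create a follow-up Rosenberg score that the described schedule does not collect.
- **The loss of sensitivity is a worst case.** A reader might take the first row of the table to mean that about two thirds of the sample is wasted. That holds only if depression does not move at all, which nothing in the document suggests. Under the same correlations the factor runs up to about 1.15. The calculation also concerns mean shifts in raw scores, whereas the plan uses relative change and a Wilcoxon test, so the factors do not carry over directly. This objection stands.
- **A BIQ given only at the end is not a flaw.** A reader might count the missing baseline BIQ as a further fault. A randomised comparison of end values, adjusted for a baseline covariate, is valid. It rules out estimating change in body image, but not a group difference. The fault is the construct.
- **The consequence is limited.** Only secondary outcomes are affected, and the Discussion states expectations without defining an outcome. This is true and limits the severity, but it does not remove the mismatch.

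**Conclusion.** The concern holds for both outcomes, more strongly for self-esteem.

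**Self-esteem:** on the protocol's own wording the follow-up instrument measures body image, and self-esteem is recorded only at baseline. No effect on it can be estimated, and the improvement expected in the Discussion cannot be shown. This rests on the article's description of when the Rosenberg scale is given.

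**Anxiety:** a difference in the overall HADS score cannot be attributed to anxiety. Relative to the anxiety part, the standardised effect on the total is about 0.54 to 0.58 if only anxiety shifts and about 1.08 to 1.15 if both parts shift equally (assumed correlation 0.5 to 0.7, equal variances, raw scores). The direction and size of the change in sensitivity are therefore unknown; the attribution problem is certain.

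This should be corrected, but it does not touch the primary endpoint or the sample size.

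**What to change.** **Anxiety.** Make the score on the HADS anxiety items the anxiety outcome, and report the depression score and the total separately. The questionnaire is already completed at baseline and at the fourth cycle, so this costs only rescoring, provided item responses are kept. The choice should be recorded before the groups are compared.

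**Self-esteem.** Report the BIQ as body image, use that one label in the objective, outcome and analysis sections, and drop the self-esteem claim from the Discussion. The cost is a narrower stated objective.

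Only if end-of-study visits are still to come is there an alternative: repeat the Rosenberg scale there and compare the groups adjusted for its baseline value, with the BIQ kept as a separate body-image outcome. That costs one short questionnaire at a visit where others are already completed. It may no longer be possible: enrolment began in June 2018, the study was to run 22 months, and analysis was planned for the second quarter of 2020.
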